#### eHealth platform

In addition to the standard care, patients in the online and device groups will have continued access to the patient platform. The Catharina BePatient website is a bariatric online module developed by BePatient™, personalized to the hospital’s standard. This company designs eHealth solutions and invents new patient pathways. In 2014 they developed an online program for bariatric patients. This encompassed shared personal health records with remote patient monitoring through wireless devices, assessment of indicators on the patients’ real life, providing a social network and coaching between healthcare professionals and patients and e-learning of selected information to raise awareness of therapeutic education. The module was complete in June 2014. Thereafter, specific questionnaires were added and personalized with color and design standards of the Catharina Hospital, resulting in the Catharina BePatient website. This website has two types of user accounts: one for the patient and one for the healthcare provider. For the latter, it can be used to modify website content and download patient data and data-traffic information. Since the start of 2015, all new patients receive registration details to create a personal account. After patients register, they are asked to sign the user agreement, which includes gathering of data and providing access to these data by the medical team. Hereafter, patients can fill in the mandatory questionnaires which are used for screening purposes, as described before. Upon completion of the questionnaires, patients are able to access additional content on the platform, depending on their stages in the treatment. A variety of content can be found on the platform, including: dietary tips; how to use medication; frequently asked questions; obesity-related facts; instruction videos of several physical exercises; and more. Users can also make a list of their eating habits which they can bring to the next appointment. Regularly, the information is revised by healthcare professionals of the Catharina Hospital to make sure information is up-to-date. Furthermore, new information and lectures are added frequently.

#### Self-monitoring devices

In addition to standard care and access to the eHealth platform, patients in the device group also have access to four wireless telemonitoring devices: a weighing scale; a blood pressure meter; oxygen saturation meter; and an activity bracelet. All devices are connectable with most smartphones and tablets using Bluetooth. By doing this, they can view their measurements on dedicated mobile applications. This can be displayed as a list of measurements or in a graph. By doing this they can track their progress in, for instance, weight loss. Patients can also set goals to achieve, for instance, a total number of steps or distances walked. These measurements are also visible on their platform accounts once they synchronize the devices to their BePatient accounts. This gives the research team insight in the frequency of use of the devices.

## Assessment of study outcomes

### Primary outcome measure

#### BMI

The primary outcome measure will be BMI. BMI is calculated with the formula: weight in kg / (height in m)^2^ = kg/m^2^. BMI is recorded through the whole follow-up scheme of five years which is standard care in this hospital. The weight of participants will be measured on calibrated electronic clinical weighing scales while fully clothed (without jackets or other items which can be removed quickly). For this study, BMI will be reported at one and two years postoperatively.

### Secondary outcome measures

#### Co-morbidity status

Co-morbidity status of diabetes mellitus type 2, hypertension, dyslipidemia, obstructive sleep apnea syndrome, gastro-esophageal reflux disease, and arthralgia is assessed at baseline and at one and two years postoperatively. A co-morbidity is considered in remission if patients do not experience any complaints and if no medication was needed since their last visit. When patients experience fewer complaints or require less medication, the co-morbidity is considered improved. If no changes are seen or when the co-morbidity worsens, it is regarded as unimproved.

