## Methods/design

### Study aim

The aims of the BePatient trial are to assess the value of eHealth by comparing different levels of telehealth provided to bariatric patients. It is hypothesized that the more eHealth is provided, the higher postoperative weight loss will be, the less likely additional contacts/visits will be consumed, the higher the patients’ satisfaction will be, and the more benefits in co-morbidity will be found. The addition of eHealth provides the patients more self-control, which could result in better commitment to the follow-up program. The primary study hypothesis is that the benefit of adding eHealth to a bariatric care program would lead to a larger reduction in body mass index (BMI) two years after the procedure compared to standard care.

Two main research questions are addressed:Does an eHealth platform increase weight loss after bariatric surgery?Does providing patients with electronical wireless monitoring devices lead to more weight loss?

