### Study setting

This open-label randomized controlled trial is conducted at the Catharina Hospital Eindhoven, a large teaching hospital in the Netherlands. Around 1000 bariatric procedures are performed annually by dedicated bariatric surgeons.

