### Inclusion criteria

The inclusion criteria to participate in this study are:Completed the mandatory questionnaire online;Having ongoing access to the Internet;Ability to use a model of mobile device (smartphone or tablet);A BMI > 40 kg/m^2^ or > 35 kg/m^2^ with related co-morbidity (hypertension, diabetes type 2, hyperlipidemia, obstructive sleep apnea syndrome, or arthralgia of lower limbs;A primary gastric sleeve or bypass planned;Age ≥ 18 years;Ability to read and write the Dutch language; andSigned informed consent.

Those who did not met the abovementioned inclusion criteria were excluded.

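### The co-morbidity rule names medication as the only treatment, so sleep apnea controlled by a breathing device can be scored as remission, and a stable device user fits two categories at once

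*Protocol article*

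**What the plan says.** Under Co-morbidity status, the protocol article lists six conditions scored at three times. The list ends with "obstructive sleep apnea syndrome, gastro-esophageal reflux disease, and arthralgia is assessed at baseline and at one and two years postoperatively". Three categories follow, identical for all six conditions:

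- Remission: "A co-morbidity is considered in remission if patients do not experience any complaints and if no medication was needed since their last visit".
- Improved: "When patients experience fewer complaints or require less medication, the co-morbidity is considered improved".
- Unimproved: "If no changes are seen or when the co-morbidity worsens, it is regarded as unimproved".

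Medication is the only treatment that the rule names. The article nowhere mentions non-drug treatment of a co-morbidity, and it gives no order of precedence between the categories.

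Sleep apnea patients enter by design, because the Inclusion criteria accept a lower BMI with "related co-morbidity (hypertension, diabetes type 2, hyperlipidemia, obstructive sleep apnea syndrome, or arthralgia of lower limbs". The Study aim makes co-morbidity a between-arm hypothesis: the more eHealth, "the more benefits in co-morbidity will be found".

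**The concern.** Obstructive sleep apnea can be treated with a night-time breathing device. A rule that asks only about complaints and medication does not see that treatment. Two patients can give the same answers at one year, one because the disease has resolved and the other because a device controls it.

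Co-morbidity reduction is a named secondary outcome, so two things are at stake: the reported sleep apnea remission rate in each arm, and the comparison of that rate between arms. A gap in the definition of treatment is also not closed by adding laboratory or blood-pressure criteria for other conditions.

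**Working it through.** **1. The plan's own figure.** The article states no figure for co-morbidity remission. Its only calculation is for BMI: difference 4, SD 8, 96 controls and 48 experimental patients, power 0.8, two-sided 5%. With the normal approximation, 4 / (8 × √(1/96 + 1/48)) = 2.83, and 2.83 − 1.96 = 0.87, which gives power 0.807 (0.802 with the t distribution). Allowing for 4% missing data, 48/0.96 = 50 and 96/0.96 = 100. The figure reproduces and does not depend on the co-morbidity rule.

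**2. The rule applied to sleep apnea patients.** All are complaint-free without drugs at one year.

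| Patient | Baseline | One year | Remission wording met? | Unimproved wording met? |
|---|---|---|---|---|
| 1 | Complaints, no device | Device started | Yes | No, complaints changed |
| 2 | No complaints, on device | Same device, nothing changed | Yes | Yes, no change seen |
| 3 | No complaints, on device | Device no longer needed | Yes | Unclear: no change in complaints or medication |

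Patient 1 is the clear case: treatment was added, and the score is remission. Patient 2 gets two contradictory scores. Patients 2 and 3 have the same record on the two items that the rule uses, so the outcome cannot tell them apart.

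The improved category has a narrower gap. A patient with unchanged residual complaints who needs the device less has neither fewer complaints nor less medication.

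**3. Effect on rates and on the comparison.** Let p be the true remission rate, taken here for illustration as complaint-free without treatment. Let f be the share of patients not truly in remission who are scored as remission.

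Scored remission = p + f(1 − p).

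If f is the same in both arms, scored difference = (1 − f) × true difference.

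The article gives neither p nor f. Assume p = 40% (control) and 60% (eHealth), and let f vary:

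| f, both arms | Control | eHealth | Difference |
|---|---|---|---|
| 0 | 40% | 60% | 20 points |
| 0.1 | 46% | 64% | 18 points |
| 0.3 | 58% | 72% | 14 points |
| 0.5 | 70% | 80% | 10 points |
| 0.7 | 82% | 88% | 6 points |

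The relative risk of not being in remission stays at 0.40/0.60 = 0.667 in every row, so the shrinkage belongs to the risk-difference scale.

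If f differs between arms, the direction is open:

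- f = 0.5 control, 0.3 eHealth: 72% − 70% = 2 points.
- f = 0.3 control, 0.5 eHealth: 80% − 58% = 22 points, above the true 20.

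The value of f also depends on precedence. If unimproved prevails, patient 2 drops out of f and patient 1 remains.

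**The case against.** The strongest reply concerns the unimproved sentence. A reader might infer that the rule scores a patient with unchanged, device-treated sleep apnea as in remission. The documents do not support that, because "If no changes are seen or when the co-morbidity worsens, it is regarded as unimproved" covers this patient just as literally. The fault there is overlapping categories, not a definite false remission. This part of the reply stands. It does not reach the patient whose complaints clear on a newly started device, because there something did change.

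A reader might also infer that the rule must shrink the difference between arms. That needs equal misclassification in all arms, which nothing guarantees. The Study setting section says "This open-label randomized controlled trial is conducted at the Catharina Hospital Eindhoven", complaints are subjective, and under Self-monitoring devices only one group receives an oxygen saturation meter. This part stands too.

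The gap in the improved category is small, since fewer complaints alone is enough to qualify. All rates above are assumed, so the real effect could be negligible.

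Finally, an article condenses a full protocol that is not shown, and scoring details for each condition may be there. That carries less weight here. The article states a complete three-category rule and applies it to all six conditions, and the rule as stated gives the wrong result for patient 1.

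**Conclusion.** The point holds as a defect in a stated outcome definition. Remission of sleep apnea can be overstated, because a patient newly controlled on a breathing device meets its wording. A stable, complaint-free device user meets two opposite categories with no precedence, so two assessors could score the same patient differently.

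The arm comparison may be biased: towards zero on the risk-difference scale if misclassification is equal across arms, and in either direction if it is not. No direction should be claimed beyond that.

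The size is unknown. The conclusion assumes that some enrolled sleep apnea patients use a breathing device, and the documents give no device-use or remission rates. The worked example concerns one of six conditions within a secondary outcome. The primary BMI outcome and the sample size are unaffected.

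**What to change.** Change the outcome definition under Co-morbidity status in three ways:

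- In both the remission and the improved sentence, replace *medication* with *medication, device or other treatment for that co-morbidity*. Make clear that this means a treatment device, not the trial's self-monitoring devices.
- Record breathing-device use (yes/no) at the existing baseline, one-year and two-year assessments.
- State which category takes precedence when a patient meets both the remission and the unimproved wording.

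The criterion for each condition is for the investigators to set. The cost is some wording, one extra data item and possibly a lower reported sleep apnea remission rate. The trial is already recruiting, so baseline device use of patients already enrolled would have to be obtained retrospectively, for instance from hospital files if it is recorded there.

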### Interventions

#### Standard care

All patients will receive standard care which consists of a five-year follow-up scheme after the bariatric procedure. The first year consists of around 10 individual and three group consultations. These follow-up visits are usually at around 1, 3, 6, 8, 9, 10, 12, 16, 20, and 24 months postoperatively and include consultations with their surgeon, dieticians, physiotherapists, and obesity nurses. After the first year, visits become less frequent. If deemed necessary, additional contact can be made. During the total follow-up time, blood markers are frequently assessed.

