#### Inventory of additional support

It can be expected that some patients who are randomized in the control or online group will make use of additional support or choose to purchase or use self-monitoring devices themselves. Patients are not limited to seek additional support if they deem that necessary (i.e. mental coaching, sporting activities, Internet forums/groups, other patient platforms, and other self-monitoring devices). To gain insights into this, a yearly questionnaire will be used, which includes questions about the frequency of the use of the abovementioned additional support.

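### Co-morbidity remission is defined without any measured value, so symptom-free untreated diabetes, dyslipidemia or hypertension counts as remission, and the improved and unimproved categories overlap

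*Protocol article*

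**What the plan says.** The section Co-morbidity status lists the conditions: "Co-morbidity status of diabetes mellitus type 2, hypertension, dyslipidemia, obstructive sleep apnea syndrome, gastro-esophageal reflux disease, and arthralgia is assessed at baseline", and again at one and two years. One three-level rule then serves all six. Remission: "A co-morbidity is considered in remission if patients do not experience any complaints and if no medication was needed since their last visit". Improvement: "When patients experience fewer complaints or require less medication, the co-morbidity is considered improved". A condition that is unchanged or has worsened is unimproved.

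Four other statements bear on this:

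- Standard care, which every arm receives, includes laboratory follow-up: "During the total follow-up time, blood markers are frequently assessed". The section Data collection places blood markers in the hospital file. Its list does not include blood pressure.
- The section Self-monitoring devices gives one arm extra measurement: "patients in the device group also have access to four wireless telemonitoring devices: a weighing scale; a blood pressure meter; oxygen saturation meter", plus an activity bracelet.
- The section Study setting states that there is no blinding: "This open-label randomized controlled trial is conducted".
- The section Inventory of additional support expects that some control and online patients will "choose to purchase or use self-monitoring devices themselves".

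The section Study aim makes greater co-morbidity benefit with more eHealth part of the trial's hypothesis.

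**The concern.** Type 2 diabetes, dyslipidemia and hypertension are identified by measurement and can be present without symptoms. A rule built only on complaints and medication cannot tell resolved disease from silent disease that nobody is treating. It may even be met at baseline, since the inclusion criteria accept diabetes, hypertension and hyperlipidemia as qualifying conditions without requiring symptoms or drug treatment.

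The middle category joins two criteria with *or*, so a patient whose complaints fall while medication rises satisfies it. The same patient can be read as worsened, which is unimproved. The length of the look-back depends on when the previous visit took place, so the one-year and two-year results do not rest on the same window.

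At stake is a secondary outcome tied to a stated hypothesis. Remission percentages would be too high by an unknown amount, and some patients could be placed in either of two categories at the assessor's discretion in an open-label trial.

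**Working it through.** The plan states no expected remission rate, so there is no figure of its own to reproduce here. Its one sample-size calculation concerns BMI and does not depend on this outcome.

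**1. Remission rule applied to a concrete patient.** Take a patient with dyslipidemia at baseline whose blood markers are still abnormal at one year, who has no complaints and for whom no drug has been prescribed. Complaints: none. Medication since last visit: none. Result under the rule: remission. The same holds for symptom-free, untreated diabetes or hypertension.

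**2. Category overlap.** Take a patient with fewer complaints and more medication. The *improved* test (fewer complaints or less medication) is met through its first limb. The *unimproved* test (no change or worsening) can be met through the rise in medication. In addition, a patient in remission who had complaints at baseline has fewer complaints, so also satisfies *improved*. The article states no order of precedence.

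**3. Look-back.** The usual visits in the section Standard care include months 10, 12, 20 and 24.
- One-year assessment: 12 − 10 = about 2 months.
- Two-year assessment: 24 − 20 = about 4 months.

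Missed or additional visits change these windows.

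**4. Size of the misclassification (illustration).** Let *r* be the share whose disease has truly resolved and who meet the rule. Let *s* be the share of persistent disease that is symptom-free and unmedicated. Then

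apparent remission = *r* + (1 − *r*) × *s*, and overstatement = (1 − *r*) × *s*.

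The documents give neither *r* nor *s*, so all values below are assumptions.

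| *r* | *s* | Apparent remission | Overstatement |
|---|---|---|---|
| 0.6 | 0.2 | 0.6 + 0.4 × 0.2 = 0.68 | 8 points |
| 0.5 | 0.3 | 0.5 + 0.5 × 0.3 = 0.65 | 15 points |
| 0.4 | 0.4 | 0.4 + 0.6 × 0.4 = 0.64 | 24 points |

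Over *r* = 0.4 to 0.6 and *s* = 0.2 to 0.4 the overstatement runs from 8 to 24 points.

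**5. Could it differ by arm?** With equal true resolution, the spurious difference (device minus control) is (1 − *r*) × (*s* device − *s* control). At *r* = 0.5:

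- equal shares, 0.3 and 0.3: 0.5 × 0 = 0;
- device 0.1, control 0.3: 0.5 × (−0.2) = −10 points;
- device 0.3, control 0.1: 0.5 × (+0.2) = +10 points.

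The sign and size depend wholly on how *s* differs between arms, and the documents do not address this.

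**The case against.** **Need for medication may already reflect measurements.** The rule speaks of medication being needed, not taken. With frequent blood tests, need could be a clinical judgement based on values. That is a possible reading for diabetes and dyslipidemia, but the text does not say so, and two assessors could apply it differently. The objection softens the point without removing it.

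**Detail of this kind may sit in the full protocol or SAP.** Condition-specific cut-offs may well be there, and their absence is not the complaint. The article does not leave the definition open. It states a complete rule for all six conditions, and that rule gives the wrong answer for silent disease.

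**The categories describe change in an existing condition.** This makes it likely that analysis is intended among patients with the condition at baseline. It does not stop a patient who is untreated and symptom-free at baseline from meeting the remission rule unchanged.

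**A stronger reading.** A reader might infer that the outcome is biased against the device arm, because home readings would uncover hypertension that stays hidden in controls. The documents do not support this as a finding:

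- No section describes a review, alert or treatment pathway from home readings. The stated use by the research team is to see how often devices are used.
- Controls are followed closely, with around 10 individual consultations in the first year.
- The devices measure neither glucose nor lipids, so the mechanism could apply only to hypertension and perhaps sleep apnea.
- Own devices in the other arms would dilute any contrast.
- The direction could reverse if reassuring readings led to medication being stopped.

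**Conclusion.** The definition needs changing. Three defects follow from the text alone, without assumptions: no measured criterion for conditions that can be silent, overlapping categories, and a look-back of about 2 months at one year against about 4 months at two years on the usual schedule.

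The amount by which remission is overstated cannot be derived from the documents. The 8 to 24 points shown rest entirely on assumed values of *r* and *s*. A difference by arm in the detection of hypertension, or possibly sleep apnea, is a structural possibility given unblinded care and meters supplied to one group only. Its size and direction are unknown, and it is zero if the silent untreated share is the same in each arm.

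This concerns one secondary outcome. The BMI analysis and the sample size are unaffected.

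**What to change.** 1. **Type 2 diabetes and dyslipidemia.** Classify status at baseline, one year and two years from the blood markers already collected in all arms, together with medication status. The clinicians should set the cut-offs before analysis. The article does not name the markers, so the sponsor should confirm that they cover both conditions at these time points.
2. **Hypertension.** Do the same with clinic blood pressure if the sponsor confirms that it is routinely recorded in all arms. If it is not, report medication status only and do not call it remission.
3. **Home devices.** Do not use their readings for classification.
4. **Sleep apnea, reflux and arthralgia.** A rule based on complaints and treatment can stay. The article names no measured follow-up value for sleep apnea, so that result should be labelled as resting on complaints and treatment.
5. **Denominator.** Analyse each condition among patients who have it at baseline.
6. **Categories.** State an order of precedence so that remission, improved and unimproved are mutually exclusive, including for fewer complaints on more medication.
7. **Look-back.** Fix one window for both time points, or define status at the assessment itself.

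The cost is new wording for the outcome definition and analysis plan, plus extraction from the hospital file. The downside is some missing laboratory or blood pressure values. If clinic blood pressure is not routinely recorded, collecting it would be a new procedure in a trial that is already recruiting, which is why item 2 offers an alternative.

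### The remission look-back for co-morbidity runs from the patient's last visit, so its length depends on attendance, and worsening is pooled with no change

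*Protocol article*

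**What the plan says.** Under Co-morbidity status, the Protocol article lists six conditions whose status "is assessed at baseline and at one and two years postoperatively". It then defines three classes.

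- *Remission*: no complaints, and a medication condition that reads "if no medication was needed since their last visit".
- *Improved*: "When patients experience fewer complaints or require less medication, the co-morbidity is considered improved". The time point for the comparison is not named.
- *Unimproved*: "If no changes are seen or when the co-morbidity worsens, it is regarded as unimproved".

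The section does not define the last visit. Under Standard care, visits are "usually at around 1, 3, 6, 8, 9, 10, 12, 16, 20, and 24 months postoperatively". The schedule is not closed: "If deemed necessary, additional contact can be made". The Background acknowledges that some patients do not finish the follow-up program. The Study aim gives greater co-morbidity benefit with more eHealth as one of its hypotheses. It also expects eHealth to give patients more self-control, "which could result in better commitment to the follow-up program", and to reduce the use of extra contacts and visits.

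**The concern.** A remission criterion should ask the same question of every patient. Here the length of the medication-free period is set by when the patient last attended. Two symptom-free patients with the same medication history can be classed differently because one kept an interim appointment and the other did not.

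That matters more than usual in this trial, because the intervention is expected to act on attendance and contacts. A measurement rule that depends on something the intervention may change can differ between arms even when the patients' health does not. The outcome it feeds is a stated secondary hypothesis in an open-label trial.

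The lowest class is a separate matter. It merges patients who stayed the same with patients who got worse, so an arm in which more patients deteriorate looks the same as one in which more stay stable.

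**Working it through.** The plan gives no figure for this outcome, so there is none to reproduce. The check works out the look-back from the visit schedule.

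**Inputs.** Visit months 1, 3, 6, 8, 9, 10, 12, 16, 20 and 24 (Standard care). Assessments after surgery at 12 and 24 months (Co-morbidity status).

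**Reading A: the last clinic visit.** Look-back = assessment month − month of the previous attended visit.

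| Assessment | Visits missed | Look-back (months) |
|---|---|---|
| Year 1 | none | 12 − 10 = 2 |
| Year 1 | 10 | 12 − 9 = 3 |
| Year 1 | 9 and 10 | 12 − 8 = 4 |
| Year 2 | none | 24 − 20 = 4 |
| Year 2 | 20 | 24 − 16 = 8 |
| Year 2 | 16 and 20 | 24 − 12 = 12 |

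Within year 2, where the arms would be compared, the range is 4 to 12 months, a ratio of 12 / 4 = 3. An extra contact would shorten the window if it counts as a visit, and the text does not say whether it does.

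**Effect on classification.** A symptom-free patient meets the medication clause when the last need for medication lies further back than the window.

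- Last need at month 18, which is 24 − 18 = 6 months before the year-2 assessment. With month 20 attended, 6 > 4, so remission. With month 20 missed, 6 < 8, so not. With months 16 and 20 missed, 6 < 12, so not.
- Last need 3 months before the assessment, full attendance. At year 1, 3 > 2, so remission. At year 2, 3 < 4, so not.

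**Illustration of size.** Assume symptom-free patients who need medication intermittently at a constant rate *r* per month. The documents give no such rate, so 0.02 to 0.10 is an assumed range. The chance of a medication-free window of *w* months is exp(−*r w*).

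| *r* | *w* = 2 | *w* = 4 | *w* = 8 | *w* = 12 |
|---|---|---|---|---|
| 0.02 | 0.961 | 0.923 | 0.852 | 0.787 |
| 0.05 | 0.905 | 0.819 | 0.670 | 0.549 |
| 0.10 | 0.819 | 0.670 | 0.449 | 0.301 |

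For such a patient, missing month 20 alone lowers the chance of meeting the clause at year 2 by 0.923 − 0.852 = 0.071 up to 0.670 − 0.449 = 0.221. The artificial difference between arms in this subgroup would be that amount times the difference in the proportion who miss month 20.

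**Reading B: the last study assessment.** The year-2 window is 24 − 12 = 12 months for everyone assessed at year 1, and interim visits no longer matter. The year-1 window runs back to the preoperative baseline. Anyone who still needed medication at any time after that assessment fails, which excludes almost everyone treated at baseline, however well they are at 12 months.

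**Direction between arms, under reading A.** Better commitment means fewer missed visits, shorter windows and easier remission with eHealth. Fewer extra contacts, if these count as visits, mean longer windows and harder remission with eHealth. The Study aim expects both, so the net sign is not known.

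**The case against.** The strongest reply is that the defect is narrow, and much of that reply stands.

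- The last-visit wording governs only the medication clause of remission. A reader might carry it over to the other classes and infer that a patient who improved by year 1 and then stayed stable becomes *unimproved* at year 2. The text does not support that. The comparator there is unstated, and baseline is at least as natural a reading.
- A reader might infer that deterioration is never counted or that new disease is hidden. Worsening is counted, as *unimproved*; it is only not shown separately. New onset has no class, but all six conditions are assessed at baseline and both years, so it can be derived. Reflux is not an entry co-morbidity, but it is assessed at baseline too.
- A reader might infer a bias in favour of eHealth, or a sixfold range of look-backs. The first overlooks the expected fall in extra contacts. The second sets full attendance at year 1 against two missed visits at year 2; within year 2 the range is threefold.
- Only patients whose last need for medication falls between the shorter and the longer window are affected. Those on continuous medication, or long off it, are classed the same way.
- The Data analysis section plans repeated-measures analysis for weight-loss patterns and does not plan a comparison of co-morbidity rates between years. The change from 2 to 4 months therefore affects mainly description.
- Reading B removes the dependence on interim attendance. This is correct, but it replaces that problem with a year-1 criterion that hardly any treated patient could meet.

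It can also be said that a condensed article leaves reporting detail to the full protocol or analysis plan. That is fair for a new-onset class. It does not answer the main point, because the article states the remission rule and the pooled class outright.

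**Conclusion.** The point holds in a limited form. As written, the remission look-back has no fixed length, and neither reading of the last visit gives a sound criterion. Under the clinic-visit reading it is about 2 months at year 1 and 4 months at year 2 with full attendance, rising to 8 or 12 months at year 2 with one or two missed visits. Symptom-free patients with recent or intermittent medication can then be classed by attendance rather than by health. Because the trial expects eHealth to change commitment and contacts, the criterion could differ by arm. No direction can be claimed, and the documents do not allow the size in the trial population to be estimated. Under the study-assessment reading, year-1 remission is nearly out of reach for anyone treated at baseline.

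In addition, the three classes cannot show deterioration apart from no change.

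The look-back figures assume that the nominal visit months are kept and that the patient attends the year-1 or year-2 assessment itself. The issue concerns a secondary outcome. The primary outcome, BMI, and the sample size built on it are not affected.

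**What to change.** Amend the outcome definition under Co-morbidity status as follows.

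1. Replace the last-visit wording with one fixed look-back for remission, the same for all patients and at both years, and independent of which visits were attended.
2. Name the preoperative baseline as the comparator for *improved* and *unimproved*.
3. Report *worsened* separately from *unchanged*.
4. Derive new onset from the existing baseline, one-year and two-year assessments, among patients without the condition at baseline.

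This defines how the outcome is measured and does not touch treatment.

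The cost is small and mainly a matter of wording, since status is already assessed at the three time points. It may not be wording alone for patients already enrolled: Data collection does not list medication among the items gathered, so medication dates may have to be checked in the records.
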